### Data management and auditing

All self-reported health information will be distributed and collected using the previously described eForsk platform. Upon randomization of each participant, researchers will share an interactive document including participant name, date of birth, phone number and randomization outcome, with the Healthy Life Centre employee to which the participant belongs. In the document, the Healthy Life Centre employee will fill out the date for treatment initiation. Researchers will use this date to plan the distribution of self-report questionnaires. Each Healthy Life Centre will have their own interactive document. Each document will be password protected and shared only with the Healthy Life Centre employees involved in the study.

Upon completion of data collection, an anonymized database will be exported from eForsk, sufficiently encrypted, and stored within the NTNU file system. The participant identification key will be confidential and stored within the eForsk database, with only the project leader having access. All data storage and analysis will be conducted according to the regulations by NTNU and will follow the General Data Protection Regulation. Data will not be disclosed to researchers outside the project or transferred to other countries. A data monitoring committee will not be involved in this study, due to the minimal risks associated with the investigated intervention.

Trial conduct will be audited in line with NTNU’s guidelines. This entails the possibility of an internal quality-assuring control where project information, data management systems, formal approvals, protocol amendments, etc. may be audited. Moreover, two independent project members are employed to follow data collection and management, and to provide support to any participants experiencing issues with the data collection. These project members have regular contact with the Healthy Life Centres participating in the trial. Both the project members and the project leader are informed about withdrawals from the study, and possible adverse events are reported to the Healthy Life Centre employees by the participants.

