### Interventions

#### Group-delivered CBT-I

Participants in the intervention arm will be offered a group-delivered CBT-I treatment developed by the Norwegian Health Directorate in collaboration with the Norwegian Competence Centre for Sleep Disorders. The intervention will be provided repeatedly at the 26 centres recruited for this study. Group size varies between centres, from 5 to 15 participants per treatment group. The treatment is a first line, low-threshold service for sleep problems in primary care without the need of referral.

The intervention will follow the standardized CBT-I program, with some adaptations based on input from researchers, clinicians, and experiences of the user group. Components of the intervention are presented in Table 1.

**Table 1 Tab1:** Components of the investigated group-delivered cognitive behavioural therapy for insomnia

Session	Educational components	Group components	Homework
1	Sleep, its functions and sleep/wake regulation Prevalence, symptoms, and consequences of insomnia Using the sleep diary Relaxation technique: Herbert Benson’s relaxation response	Participants meet each other and talk about their experiences with insomnia Participants’ course expectations	Identify three sleep-related habits to target during treatment Fill out sleep diary Fill out Sleep Hygiene Index
2	Sleep hygiene advice Stimulus control Relaxation technique: Progressive muscle relaxation	Participants’ experiences with sleep diary Learning outcomes so far Implemented changes so far	Fill out sleep diary Fill out the Negative Beliefs and Attitudes about Sleep Apply sleep hygiene advice Calculate sleep efficiency in preparation for sleep restriction
3	Dysfunctional beliefs about sleep: Identification and change Principles of sleep restriction	Implemented changes and their effect so far	Fill out sleep diary Fill out an overview of how to challenge own negative thoughts about sleep Apply sleep restriction
4	Management and maintenance of own sleep Motivation for lasting change	Implemented changes and their effect so far Alternatives to dysfunctional beliefs about sleep Adapting the learning outcomes to changing life-circumstances	

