The intervention will be conducted by Healthy Life Centres employees who are physiotherapists with extensive experience and knowledge of the treatment. They have participated in a course about delivering the intervention, organized by the Norwegian Health Directorate. All have also participated in an in-person information day, held prior to the start of the RCT, where the research project and the relevant adaptations to the intervention were presented in detail, to ensure a common knowledge basis for all instructors. The meeting was recorded, and distributed to the Healthy Life Centres employees for reference.

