#### Control group

Participants in the control group will be placed on a waiting list for 6 months. They will not be restricted from seeking other forms of treatment during the waiting period, nor from using sleep medications. After the waiting period, they will have the possibility to participate in the treatment at their Healthy Life Centre, which will be offered to them by a Healthy Life Centre employee during the waiting period.

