### Assessments

Assessments will be carried out at 6 different time points during the RCT: T1, prior to the intervention; T2, immediately post-intervention; T3, 3 months post-intervention (primary outcome measurement); T4, 6 months post-intervention; T5, 1-year post-intervention; and T6, 2 years post-intervention. The primary outcome is self-reported insomnia severity assessed by the ISI. Several other outcomes will be used in analyses of secondary outcomes, moderators and exploratory mediators, resource use and work productivity, and in a mixed-method process evaluation, described below. Descriptions of all measures, objectives of their use, collected, the participant group receiving them, and the objectives of their use, are provided in Table 2.

**Table 2 Tab2:** Overview of the assessments utilized in the randomized controlled trial

Objective	Measure	Measurement timepoint	Participant group
Demographic information	Self-rated custom questions	T1	All
Primary outcome	Insomnia severity (Insomnia severity index)	Screening, T1, T2, T3, T4	
Secondary outcomes	Health-related quality of life (EuroQol EQ5D-5L)	T1, T2, T3, T4	
	Fatigue (Chalder Fatigue Scale)	T1, T2, T3, T4	
	Mental distress (Hopkins Symptoms Checklist)	T1, T2, T3, T4	
Moderator	Chronotype (Brief Horne-Östberg Morningness-Eveningness Questionnaire)	T1, T2, T3, T4	
Mediators	Unhelpful beliefs about sleep (Dysfunctional Beliefs and Attitudes about Sleep questionnaire-16)	T1, T2, T3, T4	
	Sleep reactivity (Ford Insomnia Response to Stress Test)	T1, T2, T3, T4	
Subjective assessment of sleep patterns	7-day sleep diary	T1, T2, T3, T4	
Mixed-method process evaluation of facilitators and barriers of participants’ treatment adherence in group-delivered CBT-I	Motivation for treatment (Nijmegen Motivation List 2)	T1	~ 60 intervention group participants
	Treatment credibility (Credibility / Expectancy Questionnaire)	T1	
	Adherence to CBT-I components (Treatment Components Adherence Scale)	T3	
	Evaluation of treatment (CBT-I evaluation scale)	T3	
	Individual semi-structured interviews	T2, T3	10–12 intervention group participants
Evaluation of sick leave rates, medication use, and healthcare services utilization	Norwegian Patient Registry	T5, T6	All intervention group participants
	Norwegian Prescription Database	T5, T6	
	National Insurance Administration	T5, T6	

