#### Process evaluation

Nijmegen Motivation List 2: The Nijmegen Motivation List 2 [28] will be used to investigate different aspects of participants’ motivation for treatment: Preparedness and active participation, distress as a consequence of participants’ problems, and doubt and reserved attitude towards treatment, its requirements, or the possibilities of benefiting from it. The questionnaire consists of 34 items, scored on a 6-point Likert scale from 1, ‘Not at all applicable’ to 6, ‘Very applicable’.

Credibility / Expectancy Questionnaire: The Credibility / Expectancy Questionnaire [29] asks about the improvements that participants believe will be achieved as a result of treatment, and how believable, convincing, and logical the treatment seems. Its 6 items are scored on a numerical rating scale from 1, ‘Not at all logical’ to 9, ‘Very logical’.

Treatment Components Adherence Scale: The adherence to key behavioural and cognitive CBT-I treatment components, and their perceived benefits, will be assessed with the Treatment Components Adherence Scale [30]. Its 23 items are scored on 4-point Likert scale from 1, ‘Followed rarely or not at all’ to 4, ‘Followed consistently’.

Treatment evaluation scale: The treatment evaluation sheet [31] asks about the relevance, implementation and perceived safety of treatment. The sheet consists of 11 items scored on a 5-point Likert scale from 1, “Not satisfactory” to 5, “Very good”.

Suggestions for improvements: Participants in the intervention group will be asked, in writing, to answer open-ended questions about what worked particularly well and poorly for them during the CBT-I treatment, and their suggestions for treatment improvements.

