#### Statistical analysis plan

A detailed statistical analysis plan will be published before unblinding of study data. Descriptive statistics will be presented stratified by group allocation. Categorical and binary variables will be summarized as counts and percentages, while continuous variables as means and standard deviations or medians and interquartile range, as appropriate.

The primary outcome will be analyzed using the intention-to-treat principle. Linear mixed models will be used to estimate the mean differences between T1 and T3 in ISI with 95% confidence intervals between the two groups. For continuous secondary outcomes, linear mixed models will be utilized, while binary secondary outcomes (e.g., clinically relevant change in ISI) will be analyzed using logistic mixed models. Models will include time, group, time–group interaction and baseline covariates. Since we expect that some intervention group participants will miss some treatment sessions, per-protocol analyses will be used for individuals who complete ≥ 3 sessions. Missingness patterns will be investigated, and pattern-mixture models will be used to simulate situations where the data are not missing at random. Interim analyses will not be carried out, due to limited expected adverse effects of the treatment, and because all intervention group participants are followed up by the Healthy Life Centre employees during the treatment.

Moderation analyses will be conducted to investigate whether demographics (e.g., age, sex) chronotype, treatment group size, physical activity, length of prior insomnia treatment, and duration of insomnia moderate the effectiveness of group-delivered CBT-I on primary and secondary outcomes. Exploratory mediation analyses will be conducted to investigate mechanisms of change in the primary and secondary outcomes, focusing on psychological measures of beliefs about sleep, reactivity to stress, and sleep-related self-efficacy.

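### The only stated adverse event route is spontaneous report to treating staff, whose contact differs by arm, so adverse event counts could not be compared reliably between arms

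*Protocol article*

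**What the plan says.** The Data management and auditing section gives the rule: "possible adverse events are reported to the Healthy Life Centre employees by the participants". The same sentence says that the project members and project leader learn of withdrawals. It does not say whether adverse events are passed on to them.

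The recipients of these reports also give the treatment: "The intervention will be conducted by Healthy Life Centres employees who are physiotherapists with extensive experience and knowledge of the treatment". The Randomization section states that neither they nor the participants are masked.

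Contact with these employees is described differently for the two arms:

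- **Intervention.** There are four two-hour sessions. The Statistical analysis plan section adds that "all intervention group participants are followed up by the Healthy Life Centre employees during the treatment", and uses this as one reason for having no interim analyses.
- **Control.** "Participants in the control group will be placed on a waiting list for 6 months". The one staff contact that the Control group section describes is an employee offering the later treatment at some point in that wait.

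Table 2 lists ISI, EQ-5D-5L, Chalder Fatigue, Hopkins Symptom Check List and sleep diaries at T1 to T4. It lists no adverse event item. One process-evaluation form "asks about the relevance, implementation and perceived safety of treatment", but Table 2 gives it to about "60 intervention group participants" and only at T3.

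**The concern.** When harms are recorded only if a participant chooses to mention them, the count depends on how often the participant meets someone to tell. Here that opportunity differs by design between the randomized arms. It also shrinks once the sessions end, while questionnaire follow-up runs to 6 months after treatment. The listener is the unmasked person who gives the treatment, which may also affect what is said and what is noted.

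At stake is the harms evidence. A higher count in the intervention arm could reflect contact rather than treatment. A similar count in both arms could hide a true excess among controls, for example from deterioration during the wait. Either result would be hard to interpret in the trial report.

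**Working it through.** The article states no adverse event rate, count or analysis, so there is no figure to reproduce. The check is a comparison of sections, followed by an illustration on stated assumptions.

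**1. Opportunities to report, by arm**

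| | Intervention | Control | Section |
|---|---|---|---|
| Stated adverse event route | Tell a centre employee | Tell a centre employee | Data management and auditing |
| Scheduled meetings with those employees | Four sessions | None stated | Abstract; Control group |
| Other stated staff contact | First call about a group; follow-up during treatment | Offer of later treatment during the wait | Eligibility and procedure; Statistical analysis plan; Control group |
| Adverse event item at T1 to T4 | None listed | None listed | Table 2 |
| Symptom scales at T1 to T4 | Yes | Yes | Eligibility and procedure; Table 2 |

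The route is nominally the same in both arms. The occasions for using it are not.

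**2. Opportunities over time.** In Table 1 the homework after session 3 reads "Fill out an overview of how to challenge own negative thoughts about sleep Apply sleep restriction", and session 4 is the last. One scheduled session therefore follows the start of that component. Assessments continue at 3 and 6 months after treatment with no scheduled staff contact stated. The article does not close the route after session 4; it only stops providing occasions for it.

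**3. What unequal capture would do (illustration).** Inputs from the Sample size section: 194 intervention and 98 control participants. Assumptions that are not in the documents: a true event rate p equal in both arms, and capture probabilities c_T (intervention) and c_C (control).

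Apparent risk ratio = (p × c_T) / (p × c_C) = c_T / c_C, whatever p is.

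- c_T = 0.80, c_C = 0.80: ratio 1.0.
- c_T = 0.80, c_C = 0.40: ratio 2.0.
- c_T = 0.80, c_C = 0.10: ratio 8.0.

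The chance of a nominally significant difference (two-sided 5%, normal approximation) when the true rates are equal is about Φ[(|a − b| − 1.96 × SE0) / SE1]. Here a = p × c_T and b = p × c_C, SE0 is the pooled and SE1 the unpooled standard error. For p = 0.10 with capture 0.80 and 0.40:

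- a = 0.08, b = 0.04; expected reports 194 × 0.08 = 15.5 and 98 × 0.04 = 3.9.
- Pooled proportion = (15.52 + 3.92) / 292 = 0.0666.
- SE0 = √[0.0666 × 0.9334 × (1/194 + 1/98)] = 0.0309.
- SE1 = √[0.08 × 0.92/194 + 0.04 × 0.96/98] = 0.0278.
- (0.04 − 1.96 × 0.0309) / 0.0278 = −0.74, so the chance is about 23%.

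| True rate in both arms | Capture 80% v 40% | Capture 80% v 10% |
|---|---|---|
| 5% | 12% | 37% |
| 10% | 23% | 74% |
| 20% | 47% | 98% |

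Expected control counts are small (2.0 at p = 5% with 40% capture), so the approximation is rough. The distortion can also mask: with a capture ratio of 2.0, a true risk ratio of 0.5 would appear as 0.5 × 2.0 = 1.0.

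**The case against.** The strongest reply is that the rule is less one-sided than it may look, and several tempting readings go too far.

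- **A reader might infer that harms are seen in one arm only.** The rule says participants, without restriction by arm. Each randomized participant belongs to a centre, an employee contacts controls during the wait, and nothing bars controls from reporting. Only likely unequal capture is supported.
- **A reader might infer that harms cannot be compared at all.** Both arms complete ISI, fatigue, distress, quality-of-life and diary measures at T1 to T4, and non-responders are telephoned for ISI. A binary analysis of clinically relevant ISI change is already foreseen. Worsening on these scales can be compared as randomized, including after session 4. The limitation applies to spontaneous adverse event reports.
- **A reader might infer that reports stop at the centre employee.** The article does not say so. Project members are in regular contact with the centres, and forms and onward reporting may stand in the full protocol, which is not shown.
- **A reader might try to size the gap** from the length of the sessions, or from the roughly 60 people given the form that touches on safety. Session spacing is not stated, the route stays open afterwards, and that form is a satisfaction scale rather than an adverse event instrument. Such figures do not measure the problem.

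The article also contains other outlets. Intervention participants are asked in writing what worked poorly, dropouts may be interviewed, and people who make contact about participation burden are followed up individually. The first two exist only in the intervention arm, so they widen the imbalance. The third concerns burden and again depends on the participant's initiative.

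The reasons for having no monitoring committee and no interim analysis concern the risk of the treatment and are not hypotheses under test. The Monitoring section separately justifies the control wait. No criticism of those decisions is needed for this point.

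What remains is that the one stated route is passive, runs through treating staff, and sits on unequal contact, with no common question to balance it.

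**Conclusion.** The point holds in this limited form: as stated, adverse event capture is likely to be unequal by arm and thinner after the sessions, so counts of spontaneous reports would not support a reliable comparison between arms. The expected direction, fewer reports from controls, follows from the stated contact pattern. The size is unknown because the article gives no capture rates; the ratios of 2.0 and 8.0 only show what assumed capture gaps would produce.

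The conclusion assumes that the full protocol does not replace the stated rule with systematic questioning in both arms. It concerns harms reporting only and leaves the primary analysis of ISI at 3 months untouched. The case for change is that a better method is available at little cost.

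**What to change.** 1. Add the same short adverse event question (for example, any new or worsened health problem since the last questionnaire, and how serious it was) to the eForsk questionnaires at T2, T3 and T4 in both arms.
2. Send the answers to the project members, so that collection does not depend on contact with treating staff. Spontaneous reports to centre employees can continue, tabulated separately.
3. Report the answers by arm with the number responding at each timepoint. Beside them, give the proportion in each arm who worsened on ISI, Hopkins Symptom Check List-5 and Chalder Fatigue, with the definition of worsening fixed before unblinding. These data are already being collected.

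The cost is a slightly longer questionnaire, some non-specific reports for the project members to sort, and one extra table. Two limits remain. Answers are still unmasked self-report. They also come from responders only: at the 30% attrition assumed for sample size, about 0.70 × 292 = 204 participants. The planned telephone follow-up asks for ISI alone, so the question would have to be added to that call to reach the others.

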#### Statistical analysis plan

A detailed statistical analysis plan will be published before unblinding of study data. Descriptive statistics will be presented stratified by group allocation. Categorical and binary variables will be summarized as counts and percentages, while continuous variables as means and standard deviations or medians and interquartile range, as appropriate.

The primary outcome will be analyzed using the intention-to-treat principle. Linear mixed models will be used to estimate the mean differences between T1 and T3 in ISI with 95% confidence intervals between the two groups. For continuous secondary outcomes, linear mixed models will be utilized, while binary secondary outcomes (e.g., clinically relevant change in ISI) will be analyzed using logistic mixed models. Models will include time, group, time–group interaction and baseline covariates. Since we expect that some intervention group participants will miss some treatment sessions, per-protocol analyses will be used for individuals who complete ≥ 3 sessions. Missingness patterns will be investigated, and pattern-mixture models will be used to simulate situations where the data are not missing at random. Interim analyses will not be carried out, due to limited expected adverse effects of the treatment, and because all intervention group participants are followed up by the Healthy Life Centre employees during the treatment.

Moderation analyses will be conducted to investigate whether demographics (e.g., age, sex) chronotype, treatment group size, physical activity, length of prior insomnia treatment, and duration of insomnia moderate the effectiveness of group-delivered CBT-I on primary and secondary outcomes. Exploratory mediation analyses will be conducted to investigate mechanisms of change in the primary and secondary outcomes, focusing on psychological measures of beliefs about sleep, reactivity to stress, and sleep-related self-efficacy.

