**Methods:**

A pragmatic multicentre randomized controlled trial will be conducted with about 300 participants recruited across 26 Healthy Life Centres in Norway. Participants will complete online screening and provide consent before enrolment. Those who meet the eligibility criteria will be randomized to a group-delivered CBT-I or to a waiting list according to a 2:1 ratio. The intervention consists of four two-hour sessions. Assessments will be performed at baseline, 4 weeks, 3- and 6 months post-intervention, respectively. The primary outcome is self-reported insomnia severity at 3 months post-intervention. Secondary outcomes include health-related quality of life, fatigue, mental distress, dysfunctional beliefs and attitudes about sleep, sleep reactivity, 7-day sleep diaries, and data obtained from national health registries (sick leave, use of relevant prescribed medications, healthcare utilization). Exploratory analyses will identify factors influencing treatment effectiveness, and we will conduct a mixed-method process evaluation to identify facilitators and barriers of participants’ treatment adherence. The study protocol was approved by the Regional Committee for Medical and Health Research ethics in Mid-Norway (ID 465241).

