## Background

Insomnia is the most common sleep disorder in the general population and in clinical practice [1], with ~ 10% of adults reporting chronic insomnia in agreement with the current diagnostic classification system [2] and seems to be on the rise [3]. Among patients seeking primary care, as many as 50–70% report disturbed sleep [4, 5]. Cognitive behavioural therapy for insomnia (CBT-I) is considered most effective for long-term alleviation of chronic insomnia [6–8], but administration of CBT-I is limited by a lack of trained therapists and long waiting lists [9] (i.e., up to 1 year in Norway). To increase the availability of CBT-I, a group-delivered treatment was developed by the Norwegian Health Directorate. The treatment is based on core CBT-I principles including sleep hygiene, stimulus control, sleep restriction, cognitive restructuring, and relaxation training. Group-delivered CBT-I may complement individual CBT-I and relieve pressure on primary care, as group size may include up to 15 individuals at the same time. Although group-delivered CBT-I has already been implemented in several municipalities in Norway, its effectiveness has never been evaluated. Therefore, the objective of this study is to investigate the effectiveness of group-delivered CBT-I in Norwegian primary care.

It is of interest to identify factors that may influence the therapeutic response of group-delivered CBT-I. Up to 40% of insomnia patients do not adequately respond to CBT-I [10], likely due to insomnia heterogeneity [10–12]. For instance, insomnia patients with evening chronotype, unhelpful beliefs about sleep, short sleep, comorbidity, or high reactivity to stress may have a blunted response to CBT-I [12–15], possibly due to the influence of overactive neurobiological and psychological systems in insomnia pathophysiology [16]. Adherence to the therapeutic regime may also predict outcome [17]. Thus, a secondary objective of this study is to conduct exploratory analyses to identify factors influencing the effectiveness of group-delivered CBT-I.

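### The per-protocol comparison selects on attendance in the intervention arm only, so it is open to selection bias, plausibly but not necessarily upward

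*Protocol article*

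**What the plan says.** The Statistical analysis plan section of the protocol article fixes the main approach: "The primary outcome will be analyzed using the intention-to-treat principle". It then adds a second analysis and its reason: "Since we expect that some intervention group participants will miss some treatment sessions", "per-protocol analyses will be used for individuals who complete" at least 3 sessions. The Abstract gives the length of the course: "The intervention consists of four two-hour sessions". On adjustment, the plan says "Models will include time, group, time–group interaction and baseline covariates", without naming the covariates.

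For the other arm, the Control group section says "Participants in the control group will be placed on a waiting list for 6 months". The Background adds, among factors that may influence response to the therapy, that "Adherence to the therapeutic regime may also predict outcome".

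The article does not say which controls enter the per-protocol comparison, and it names no counterpart of the session rule for them. A detailed SAP is announced for publication before unblinding.

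**The concern.** A rule of at least 3 sessions can remove people only from the arm that is offered sessions. Intervention participants who attend 0 to 2 sessions drop out of the analysis. Controls who would have attended as little, had they been offered the course, stay in. The two groups compared are then no longer those that randomisation created.

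If attenders and non-attenders would have had different insomnia severity at T3 without any treatment, that difference enters the estimate as if it were a treatment effect. This is the only analysis the article states for the effect of completing the course, so a reader may take it as that effect.

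Adjustment for baseline covariates may remove part of the difference but cannot be relied on to remove all of it. Table 2 lists treatment motivation and credibility, two natural predictors of attendance, for about 60 intervention participants only and for no controls. The arms therefore cannot be balanced on them.

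**Working it through.** **Inputs from the article**
- Planned effect 0.50 SD, 2:1 allocation, two-sided 5%, 90% power, stated total 192 (Sample size). This reproduces: 64 + 128 = 192, power 0.901. No figure is stated for the per-protocol analysis, so 0.50 SD serves only as a yardstick.
- Final sample 292 (98 control, 194 intervention) with 30% attrition. 292 × 0.7 = 204.4, or about 68 controls and 136 intervention participants analysed.
- ISI changes of 6.2 and 1.4 points with d = 0.86. The implied SD is (6.2 - 1.4)/0.86 = 4.8/0.86 ≈ 5.6 points.

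**Assumptions, not in the documents**
- q, the share of the intervention arm completing at least 3 sessions: 0.6 to 0.9.
- g, the gap in untreated T3 outcome between would-be attenders and non-attenders: -0.5 to +0.5 SD. Positive means that attenders do better.

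**Size of the bias.** The untreated mean of a whole arm is q × (attender mean) + (1 - q) × (non-attender mean). Subtracting this from the attender mean gives

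bias = (1 - q) × g.

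| q | g = -0.5 | g = -0.3 | g = 0 | g = +0.3 | g = +0.5 |
|---|---|---|---|---|---|
| 0.6 | -0.20 | -0.12 | 0 | +0.12 | +0.20 |
| 0.7 | -0.15 | -0.09 | 0 | +0.09 | +0.15 |
| 0.8 | -0.10 | -0.06 | 0 | +0.06 | +0.10 |
| 0.9 | -0.05 | -0.03 | 0 | +0.03 | +0.05 |

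At q = 0.7, a bias of 0.09 to 0.15 SD in either direction is 18% to 30% of 0.50, or about 0.5 to 0.8 ISI points (0.09 × 5.6 and 0.15 × 5.6).

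**Second route.** Let ρ be the correlation between the propensity to attend and untreated improvement. Then bias = ρ × φ(z_q)/q. At q = 0.7 this gives ±0.15 SD for ρ = ±0.3 and ±0.05 SD for ρ = ±0.1, in line with the table. Suppose a true effect of 0.50 SD in attenders and none in non-attenders. A simulation of 2,000,000 subjects then gives, at q = 0.7:

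| ρ | Intention to treat | Attenders vs all controls | Complier average (ITT/q) |
|---|---|---|---|
| -0.3 | 0.35 | 0.35 | 0.50 |
| -0.1 | 0.35 | 0.45 | 0.50 |
| 0 | 0.35 | 0.50 | 0.51 |
| +0.1 | 0.35 | 0.55 | 0.50 |
| +0.3 | 0.35 | 0.65 | 0.50 |

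**False positives.** With no treatment effect at all and q = 0.7, the unadjusted test of attenders against all controls (136 vs 98) rejects in 20.1% of trials at ρ = ±0.3 and in 6.6% at ρ = ±0.1, against a nominal 5%. After 30% attrition the figures are 15.5% and 6.1%.

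**Precision, 68/136 analysed, q = 0.7**
- Attenders vs controls: 136 × 0.7 ≈ 95 attenders; √(1/68 + 1/95) = 0.16 SD.
- Complier average: √(1/68 + 1/136)/0.7 = 0.149/0.7 = 0.21 SD; about 0.22 in simulation.

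**Check on the alternative.** The complier average is unbiased above only because non-attenders were given no effect. Assume instead 70% full attenders with effect 0.50 and 25% partial attenders with half of it. Then ITT = 0.7 × 0.50 + 0.25 × 0.25 = 0.4125, and 0.4125/0.7 = 0.59, which is 0.09 too high for full attenders. With any attendance as the exposure, 0.4125/0.95 = 0.43, the true average effect among those who attend at all.

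**The case against.** A reader might infer that the per-protocol analysis overstates the effect. The documents do not support that as a certainty. The Background remark on adherence concerns response to the therapy, and a plain dose effect would produce the same association. It says nothing about how attenders would fare untreated. If people who improve early stop coming, the bias reverses. If sessions are missed for scheduling reasons, it may be near zero. This part of the objection stands, so the range must include zero and negative values.

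The formulas also describe a raw comparison at T3. The planned mixed models use T1 and baseline covariates, and only the gap that remains after adjustment counts. This stands too: the figures are before adjustment.

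A reader might also conclude that a complier-average estimate should replace the per-protocol one. That goes too far. Table 1 places sleep hygiene, stimulus control and both relaxation techniques in sessions 1 and 2, so partial attenders receive core components. Participants are unmasked and ISI is self-reported, so allocation itself may move the outcome. Both strain the exclusion restriction, and the check above shows an upward bias of 0.09 SD under one plausible pattern.

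Finally, intention-to-treat governs the primary outcome, the per-protocol analysis has no confirmatory role, and the comparator set and covariates may be settled in the SAP. That limits the weight of the point but does not remove it. The attendance rule is stated now, and no choice of controls can apply the same observed filter to people who were offered no sessions.

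**Conclusion.** The point holds as a risk of selection bias of uncertain direction. The rule of at least 3 sessions acts after randomisation and in one arm only, so the comparison lacks the protection of randomisation. With 70% attendance and an untreated gap of -0.5 to +0.5 SD, the bias lies between about -0.15 and +0.15 SD, and is zero without a gap. An upward bias is plausible, since motivated people may both attend and improve, but nothing in the documents establishes it.

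The size rests on an assumed attendance share and gap, on a comparison before baseline adjustment, and on the strong but unstated inference that all controls are the comparator. The primary conclusion is not at stake. The plan should be changed so that this comparison is not read as the effect of receiving the course.

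**What to change.** In the SAP, before unblinding:
- Keep intention-to-treat as primary.
- Label the comparison based on at least 3 sessions as supportive and open to selection bias in either direction, and do not report it as the effect of receiving the course.
- Add a complier-average causal effect for T3 ISI, with randomised arm as the instrument for completing at least 3 sessions (for example by two-stage least squares), adjusted for baseline ISI and centre. It must use all randomised participants. That includes intervention participants who cannot fit the offered group, whom the Eligibility and procedure section excludes after allocation.
- State the exclusion restriction openly: allocation affects ISI only through completing at least 3 sessions. Because fewer sessions may have some effect and participants are unmasked, repeat the analysis with any attendance (at least 1 session) and with number of sessions (0 to 4) as the exposure.

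The cost is SAP wording and a few lines of code, using attendance data that the existing rule already requires. The statistical price is a wider interval (standard error about 0.22 against 0.16 SD at 70% attendance with 68/136 analysed) and an assumption that must be defended.
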